
#### Neighborhood indices

The composite Healthy Neighborhood Index (HNI) is calculated as the average of the weighted standardized scores for the four domains or sub-indices (i.e., green environment, neighborhood SES, social environment, and walk friendly) converted to a standard normal percentile. The HNI is intended to capture the multidimensional nature of neighborhood-level factors associated with ADRD risk that cannot be explained by a single variable or a group of variables within a single domain. Data normalization is essential in composite indices as the underlying variables are often measured at different scales or units of analysis. A standard z-score calculation is used to normalize the data for the HNI composite score. Since z-score standardization requires data to be approximately normally distributed, univariate analysis is performed to identify variables with a skewed distribution and the presence of outliers. Scatter plots, box plots, or the Grubbs statistical test are employed to identify outliers. Log-10, natural log, square root, or the inverse normal method are common transformations used to create a new variable as a function f(X) of the original variable. The underlying variables for each domain or sub-index are examined for directional effect, and the z-score computation is adjusted to account for those effects. Weighting the underlying variables of each sub-index is an important consideration when different variables may have dissimilar effects on the neighborhood-level ADRD risks. In this study, we derive weights from Principal Component Analysis (PCA), specifically the component loadings matrix (post-rotation) representing the total unit ratio of explained variance for each variable loaded on a component. We compute a sub-index score for each of the four domains as the average of the underlying variables z-scores. The overall HNI index score is calculated by averaging the standard normal percentile of the four sub-components. Ordinary least squares regression analysis will be performed to gauge the internal validity of the HNI, where the HNI score will be used as the dependent variable and the four sub-indices as independent variables.

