### Neighborhood social and built environment variables

Neighborhood social and built environments at the residential Census block group level will be captured with 4 domain indices (green environment, neighborhood socio-economic status, social environment, walk-friendly design) and a summary Healthy Neighborhood Index (HNI). Domain categories were determined *a priori* as they are major neighborhood-level constructs associated with ADRD risk factors and disease risk in prior studies (citations). These measures will be calculated for the baseline visit year and following years, accounting for changes in residential address and changes in neighborhood environments, as applicable. ArcGIS Pro will be used to calculate and map these objective geographic information systems (GIS) measures.

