### Green environment

Percentage of tree canopy: Tree canopy data obtained from the U.S. Forestry Service will be used to calculate the percentage of the block group comprised of tree canopy (i.e., percentage of tree coverage of the ground provided by tree leaves, branches, needles, and stems).Mean normalized difference vegetation index (NDVI) will be calculated for each participant’s neighborhood for the burn and non-burn periods based on satellite imagery available from the U.S. Geological Survey (USGS, Landsat 8 Level 2, Collection 2, Tier 1). The NDVI scale is -1 to +1 (more positive measures = healthier vegetation/”greener”) and is calculated as follows: NDVI = (R_NIR_-R_RED_)/(R_NIR_+R_RED_). R_NIR_ is reflectance in near-infrared (0.86–0.88mm) and R_RED_ is reflectance in red (0.64–0.67mm). Reflectance values are captured in 30x30 meter Landsat satellite images. Mean NDVI will be calculated for participants’ Census block group. This global measure of the density of healthy vegetation captures all types of greenery including purposefully-built greenspaces (e.g., park/open spaces, street plantings, and yards) and those in natural and rural environments (e.g., forests, farms, and uninhabited areas), and has been linked to multiple ADRD risk factors and outcomes.Percentage open space: National Land Cover Dataset (NLCD) will be acquired through the Multi-Resolution Land Characteristics Consortium, to calculate the percentage of open space in the block group. The NLCD uses 30-meter spatial resolution satellite imagery to characterize land and surface uses and types, such as developed land, barren land, deciduous forest, scrub, and wetlands. Developed open space includes mostly vegetation/grasses (<20% impervious surfaces) found in parks, large family lots, planted vegetation for recreation or erosion control, and golf courses.Percentage park space, distance to nearest park, and number of parks: We will calculate the percentage of the block group comprised of park space using combined data from the Florida Geographic Data Library’s Areas of Interest layer for Florida Parks and Recreational Facilities and ESRI’s ArcGIS Online data layer “USA Parks” (covers state parks). Distance in miles from the residence to the nearest park and number of parks in the block group will be calculated based on the same park data sources.

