#### Aim 2A

General linear mixed model analyses of participants nested within neighborhoods (i.e., census block groups) will be used to examine the effect of built and social environments on CF and SI for Aim 2A. Primary analysis will model effects of the four domains of social and built environment and the HNI on baseline CF and SI and on changes over 36 months, accounting for random neighborhood-level variance. Both time-varying (e.g., health behaviors, work and home environments, comorbidities) and time-invariant (e.g., sex) individual- and neighborhood-level covariates (see Fig 1) will be incorporated into prediction models to control for these additional individual and neighborhood/community influences on outcomes.

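### The HNI rule takes standard normal percentiles of domain scores that are averages of z-scores, with no stated rescaling to SD 1, and the section conflicts on weighting and order of steps

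*Protocol article*

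**What the plan says.** The section on neighborhood social and built environment variables in the protocol article sets up "4 domain indices (green environment, neighborhood socio-economic status, social environment, walk-friendly design) and a summary Healthy Neighborhood Index (HNI". These are the Aim 2 exposures: "Primary analysis will model effects of the four domains of social and built environment and the HNI on baseline CF and SI". Aim 2B then tests their interaction with race/ethnicity.

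The Neighborhood indices section builds them as follows.

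- **Opening definition.** The HNI is "calculated as the average of the weighted standardized scores for the four domains or sub-indices", converted to a standard normal percentile.
- **Normalisation.** "A standard z-score calculation is used to normalize the data for the HNI composite score". The reason given is that the underlying variables have different scales, so the z-scoring acts on the variables.
- **Weights.** "we derive weights from Principal Component Analysis (PCA), specifically the component loadings matrix (post-rotation").
- **Sub-index.** "We compute a sub-index score for each of the four domains as the average of the underlying variables z-scores". This sentence names no weight.
- **HNI.** "The overall HNI index score is calculated by averaging the standard normal percentile of the four sub-components".

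No sentence says that a sub-index is brought back to mean 0 and SD 1 before its percentile is taken.

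**The concern.** The standard normal distribution function returns a percentile only for a score with mean 0 and SD 1. Each variable meets that after z-scoring, but an average of several such variables does not. Averaging shrinks the spread, by an amount that depends on how many variables the domain has and how strongly they correlate.

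Two things follow if the rule is applied as written. The values called percentiles crowd towards 50. The domains also lose spread unequally, so an average meant to count four domains alike gives more influence to those with fewer or more closely related variables.

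The section also describes the HNI in two ways that do not agree. The opening sentence has weighted, standardised domain scores, and it can be read as averaging before conversion. The later sentences have averages of variable z-scores, converted domain by domain and then averaged. Two analysts could build different indices from this text.

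The planned check, which regresses the HNI on its own four sub-indices, would not reveal the problem. The HNI is constructed from those sub-indices, so the fit will be close either way.

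**Working it through.** The article gives no HNI value, sub-index SD or domain weight, so there is no figure of the plan's own to reproduce.

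**Inputs**

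- Number of variables per domain, k. This is a count from the four domain sections, since the article gives no totals. For example, one green entry, "Percentage park space, distance to nearest park, and number of parks", supplies three variables. The counts are about 6 green, 6 SES, 9 social and 12 walk-friendly (13 if the intersection measures are split further).
- Mean correlation between variables within a domain, r, after aligning their direction. It is not given and is assumed, mainly from 0.1 to 0.5.
- For HNI variances, domains are taken as independent and scores as normal. Both are assumptions.

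**Step 1: SD of a sub-index.** SD = sqrt((1 + (k − 1)r)/k), which equals 1 only if r = 1. For k = 6 and r = 0.3: sqrt((1 + 5 × 0.3)/6) = sqrt(2.5/6) = 0.645.

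**Step 2: score of a block group truly at the 90th percentile.** Score = Φ(1.2816 × SD). For SD 0.645: Φ(0.827) = 0.796.

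| r (all domains) | SD: green / SES / social / walk | True 90th percentile scores as |
|---|---|---|
| 0.1 | 0.50 / 0.50 / 0.45 / 0.42 | 0.74 / 0.74 / 0.72 / 0.70 |
| 0.3 | 0.65 / 0.65 / 0.62 / 0.60 | 0.80 / 0.80 / 0.79 / 0.78 |
| 0.5 | 0.76 / 0.76 / 0.75 / 0.74 | 0.84 / 0.84 / 0.83 / 0.83 |
| 0.9 | 0.96 / 0.96 / 0.96 / 0.95 | 0.89 in each |

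**Step 3: spread of the HNI.** For S ~ N(0, s²), Var[Φ(S)] = arcsin(s²/(1 + s²))/(2π). With s = 1 this is 1/12, so four independent re-standardised domains give an HNI SD of sqrt(4/12)/4 = 0.144. As written:

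- r = 0.1: the SDs of Φ(S) are 0.179, 0.179, 0.163 and 0.154. The HNI SD is sqrt(0.0320 + 0.0320 + 0.0266 + 0.0237)/4 = 0.085, and 0.144/0.085 is about 1.7.
- r = 0.3: the SDs are 0.218, 0.218, 0.210 and 0.206. The HNI SD is 0.107, a ratio of about 1.35.
- r = 0.5: the SDs are 0.245, 0.245, 0.241 and 0.239. The HNI SD is 0.121, a ratio of about 1.2.

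A coefficient per HNI point changes by about the same factor.

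**Step 4: effective domain weights.** Each domain's share is its Var[Φ(S)] divided by the sum over domains.

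| Assumed r: green / SES / social / walk | Share of HNI variance |
|---|---|
| 0.3 in all | 26 / 26 / 24 / 23% |
| 0.15 / 0.45 / 0.08 / 0.25 | 23 / 37 / 16 / 24% |
| 0.3 / 0.6 / 0.1 / 0.3 | 26 / 36 / 15 / 23% |

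After each sub-index is divided by its own SD, simulated shares are 24.9 to 25.0%, and the true 90th percentile scores 0.90 in every domain.

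**Step 5: do PCA weights rescue it?** Not if they are non-negative and sum to 1. Under a common correlation r, SD = sqrt(r + (1 − r)Σw²). Example weights 0.30, 0.25, 0.20, 0.10, 0.10 and 0.05 have Σw² = 0.215. The SD is then 0.54, 0.67 and 0.83 at r = 0.1, 0.3 and 0.6.

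**Step 6: does the order of steps matter?** Take domain z-scores of 2, 0, 0 and 0. Converting and then averaging gives (0.977 + 3 × 0.5)/4 = 0.619. Averaging and then converting gives Φ(0.5) = 0.691. Averaging un-rescaled sub-indices and converting once compresses more. With r = 0.15/0.45/0.08/0.25, the 97.5th-percentile block group scores at about the 71st percentile if domains are independent, and at about the 78th if they correlate at 0.3.

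**Step 7: does it change the ordering?** Φ is monotone, so ranks within a domain stay the same. With r = 0.3/0.6/0.1/0.3, the simulated HNI with and without rescaling correlates at 0.983.

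**The case against.** The strongest reply is that the opening sentence speaks of standardised scores for the four domains. That may mean the domain scores are themselves standardised, with the step simply not repeated, and an article may leave such detail to a fuller document. Part of this stands: the text does not prove that un-rescaled averages will be used. It does not dispose of the point, because the later and more specific sentence defines the sub-index, and the next one takes its percentile. That is a stated rule which misfires when followed, not merely an omitted detail.

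Several stronger conclusions that a reader might draw are not supported.

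- **That reported percentiles are wrong.** The article reports none.
- **That the sub-indices are certainly plain averages.** The same section derives PCA weights. Step 5 shows that weights summing to 1 leave the SD below 1, but the exact SDs and shares would differ from those for unweighted averages.
- **That SES will dominate the HNI.** SES counts 2.3 times social (37/16) only under one set of assumed correlations. Equal correlations of 0.3 give shares of 23 to 26%. The article promises an average of four components, not equal shares of variance, and the 25% benchmark itself assumes independent domains.
- **That Aim 2 coefficients are biased, or that domain effects will be compared per percentile.** Aim 2A names no unit. A linear change of scale alters a coefficient's unit, not its test or fit.

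**Conclusion.** The point holds in limited form. The Neighborhood indices section gives a rule that, followed as written, does not yield percentiles, and it conflicts with its own opening sentence on weighting and on order of steps.

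That the SD falls below 1 is certain for any non-negative weighting that sums to 1, short of perfect correlation. The size rests on counted k and assumed r. For r between 0.1 and 0.5, a true 90th percentile scores at about the 70th to 84th, and the HNI SD shrinks about 1.2- to 1.7-fold. Unequal domain weighting is slight if r is similar across domains and material only if it differs. Differing r is plausible, since the social domain mixes crime, ethnic composition, household size and counts of churches, while the SES inputs are mostly economic and housing measures.

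Because ranks within a domain are kept and the two versions of the HNI correlate at about 0.98 or higher, tests should change little. What suffers is the meaning of an HNI point, the comparability of any percentile-scaled domain effects, and the reported effect size. These are primary Aim 2 exposures and the repair is cheap, so it should be made before the indices are computed.

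**What to change.** Replace the two descriptions in the Neighborhood indices section with a single formula that states:

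1. the variable weights within each sub-index, including whether the PCA loadings are used and how they are scaled;
2. that each sub-index is re-standardised to mean 0 and SD 1 over the study block groups, or replaced by its empirical percentile rank, before any percentile conversion;
3. whether conversion comes before or after averaging over the four domains;
4. that the composite is treated in the same way if it is itself expressed as a percentile.

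Report Aim 2 domain and HNI effects per SD of the re-standardised score. The cost is a few sentences in the index definition and about one line of code. No new data are needed.

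### The planned validity check regresses the Healthy Neighborhood Index on the sub-indices it is built from, so it cannot measure validity, and the index's construction is stated inconsistently

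*Protocol article*

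**What the plan says.** All the construction text is in the section *Neighborhood indices* of the protocol article.

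- Opening definition: the HNI "is calculated as the average of the weighted standardized scores for the four domains or sub-indices", followed after a parenthesis listing the domains by "converted to a standard normal percentile".
- Weights: "we derive weights from Principal Component Analysis (PCA), specifically the component loadings matrix (post-rotation").
- Sub-index: "We compute a sub-index score for each of the four domains as the average of the underlying variables z-scores". No weight is named in this sentence.
- Closing definition: "The overall HNI index score is calculated by averaging the standard normal percentile of the four sub-components".
- Validity: a least squares model is meant to show how valid the index is internally. In that model, "the HNI score will be used as the dependent variable and the four sub-indices as independent variables".

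The section *Aim 2A* gives the index its role: "Primary analysis will model effects of the four domains of social and built environment and the HNI on baseline CF and SI", and on change over 36 months. The article names no criterion outside the index against which the HNI would be validated.

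**The concern.** There are two problems.

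**The check is circular.** A regression of a composite on its own components describes how the composite was calculated. It does not show whether the composite captures healthy neighborhoods. If four meaningless domains give the same near-perfect fit as four sound ones, the result carries no information on validity, yet it would be reported as validity evidence for a primary exposure.

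**The construction is not fixed.** One sentence has weighted scores, another an average with no weight. One can be read as average first and convert to a percentile afterwards, another as convert first and average afterwards. Two analysts could follow the same section in good faith and build different exposures for Aim 2. If the choice is left until outcomes are known, it could also be influenced by the results.

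**Working it through.** The article gives no numerical result for the HNI or its check, so there is no figure to reproduce.

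**Inputs.** Four domains (*Neighborhood indices*). About 50 block groups, from at least 10 in each of 5 communities (*Sample size calculations for full sample*). Assumptions not in the article: standard normal domain scores z1 to z4 with a common inter-domain correlation r of 0, 0.3 or 0.5. Φ is the standard normal distribution function.

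- Version A (average, then convert): HNI = Φ(mean of z).
- Version B (convert, then average): HNI = mean of Φ(z).

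**1. The check on percentiles.** Under B, HNI = 0.25·p1 + 0.25·p2 + 0.25·p3 + 0.25·p4 with pj = Φ(zj). Regressing it on p1 to p4 returns four slopes of 0.25 and R-squared = 1, whatever the data.

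**2. The check on z-scores.** Under B the best linear predictor is mean(z)/(2√π), so R-squared = [(1 + 3r)/4]/(4π) ÷ Var(B). Here Var(B) = (1 + 3ρ)/48 and ρ = (6/π)·arcsin(r/2).

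- r = 0: (0.25/12.566)/(1/48) = 3/π = 0.955.
- r = 0.3: ρ = 0.288, Var(B) = 0.0388, and (0.475/12.566)/0.0388 = 0.974.

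With 50 block groups and four predictors the sample value is slightly higher: 1 − (1 − 0.955)·45/49 = 0.959 and 1 − (1 − 0.974)·45/49 = 0.976. Simulation at 50 block groups agrees, with means of about 0.96 and 0.98. The shortfall from 1 is only the curvature of Φ. Over a wider set of structures, including skewed noise and domains in opposition, the means at 50 block groups ran from 0.92 to 0.9999. The lowest single run was 0.79 (35 block groups, opposed domains, re-standardized sub-indices). In no setting did the fit separate noise from structure.

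**3. Order of steps.**

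| Domain z-scores | A | B |
|---|---|---|
| (2, 0, 0, 0) | Φ(0.5) = 69.1 | (97.7 + 3×50)/4 = 61.9 |
| (2, 2, −1, −1) | Φ(0.5) = 69.1 | (2×97.7 + 2×15.9)/4 = 56.8 |
| (2.4, 0, 0, 0) | Φ(0.6) = 72.6 | 62.3 |
| (0.5, 0.5, 0.5, 0.5) | 69.1 | 69.1 |

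The last two rows swap rank between A and B. Over whole data sets the versions stay close. At 50 block groups their correlation averages about 0.98 (r = 0), 0.992 (r = 0.3) and 0.996 (r = 0.5). With sub-indices re-standardized, 5% to 25% of block groups change quintile on average, while the mean Spearman correlation is 0.96 to 0.997.

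**4. Scale.** Var(A) = arcsin(s²/(1 + s²))/(2π) with s² = (1 + 3r)/4.

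| r | SD of A | SD of B | Ratio |
|---|---|---|---|
| 0 | 0.179 | 0.144 | 1.24 |
| 0.3 | 0.228 | 0.197 | 1.16 |
| 0.5 | 0.251 | 0.226 | 1.11 |

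If the four-domain mean is first re-standardized to unit variance, the SD of A becomes √(1/12) = 0.289, and the ratio at r = 0.3 is 0.289/0.197 = 1.47. The article states no such step.

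**5. Weighting.** Weighted A against unweighted B gave mean Spearman correlations from 0.71 to 0.99 at 50 block groups. The low values (0.71 and 0.73) came from unstructured noise, 0.89 from opposed domains, and 0.975 to 0.99 from domains with coherent structure. The weights here were squared unrotated first-component loadings, an assumption; the article specifies rotated loadings. The comparison also mixes weighting with order of steps.

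**The case against.** The best defence is that this is loose wording in a condensed article. The phrase about conversion to a percentile can attach to each domain score. The opening sentence then agrees with the closing one, and the conflict over the order of steps disappears. That reading is available and stands. It does not settle the weights.

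A reader might infer that the weights are derived and never used. The text does not support that: the opening sentence calls the scores weighted, and an average need not be unweighted. What the text leaves open is where the weights enter.

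A reader might infer that the regression is a gate that would certify a bad index. The article states no threshold, decision rule or later use for it, and no Aim 1 or Aim 2 estimate depends on it. The point that stands is that the analysis cannot do what it is said to do.

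A reader might infer a 1.5-fold difference in the effect per unit of HNI. That needs the unstated re-standardization at r = 0.3. Read literally, the ratio is 1.11 to 1.24, and reporting effects per SD removes this change of units.

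A reader might infer that *Aim 2A* fits the HNI and its four domains together and is therefore collinear. That section does not say they share a model, so this is a risk to exclude and not an error in the plan. Whether the HNI should be the lead test is a matter of preference.

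**Conclusion.** The circular check is wrong as written. R-squared is exactly 1 on sub-index percentiles under the closing definition. On z-scores it averages about 0.96 to 0.98, for pure noise as for correlated domains, so it says nothing about validity. The percentile result is algebra; the z-score figures assume normal domain scores and about 50 block groups.

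The construction is inconsistently stated on weighting and ambiguous on the order of steps. The order has a modest effect: correlation about 0.98 to 0.996, and an SD ratio of about 1.1 to 1.25, or up to about 1.5 at r = 0.3 with re-standardization. The weighting choice can matter more, but its size depends on loadings that the article does not give. The defect should be corrected, but it does not in itself invalidate Aim 2.

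**What to change.** 1. Remove the regression of the HNI on its sub-indices as validity evidence. If it is kept, describe it as showing how the index is composed.
2. Replace it with the association between the HNI and variables outside it that the baseline survey (T0) already collects, for example feeling safe walking in the neighborhood in the dark, and the amount of physical activity done outdoors. These are individual self-reports, so they are only a partial criterion and should be reported as such. Physical activity may also serve as a health-behavior covariate in *Aim 2A*, which should be acknowledged.
3. State one formula before outcomes are analysed: where the principal component weights enter, whether sub-indices or their mean are re-standardized, and at which step the percentile conversion is made. One version consistent with most of the section is a weighted mean of direction-aligned z-scores within each domain, conversion of each sub-index to a percentile, then the mean of the four percentiles.
4. State in *Aim 2A* that the HNI is not entered in the same model as all four of its domains.

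The cost is a few sentences and one small analysis of data already planned. No new data collection is needed.
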